## Abstract

**Background:**

Excessive hepatic fat is associated with increased metabolic risk factors, production of inflammatory factors, and oxidative stress. High protein intake might trigger an increased hepatic lipid oxidation through an increase in hepatic energy expenditure. Furthermore, the majority of randomized controlled trials (RCT) in humans have failed to show whether carotenoids can be used to prevent and treat non-alcoholic fatty liver disease (NAFLD). However, it is notable and contradictory that NAFLD is rapidly escalating in Iran and other countries with lower intakes of fruit and vegetables (as sources of β-cryptoxanthin [β-CX] and carbohydrates) and higher intake of carbohydrates (as an agent of NAFLD); and the effects of β-CX and a high protein diet (HPD) on NAFLD need to be investigated further.

**Methods/design:**

This study will be conducted as a randomized, double-blind, placebo-controlled clinical trial for 12 weeks to receive daily β-CX 6 mg supplementation combined with a HPD on levels of metabolic factors, β-CX, glycemic and lipid profiles, inflammatory factors, adipocytokines, and body composition. Ninety-two eligible patients, aged 18–60 years, of both genders, who are obese and overweight (body mass index [BMI] 25–40 kg/m^2^) will be randomly assigned to four groups as follow: HPD + placebo; normal protein diet + β-CX (NPD + β-CX); HPD + β-CX; and NPD + placebo (control group). Two populations will be analyzed in this work. The intention-to-treat (ITT) population includes all patients who will be randomized, while the per-protocol (PP) population includes all individuals who complete the 12- week intervention (i.e. study completers).

**Discussion:**

Our findings from this trial will contribute to the knowledge of the relationship between β-CX supplementation and a HPD on NAFLD patients and determination of optimal macronutrient ratios without energy restriction.

**Trial registration:**

Iran clinical trials registry, IRCT2017060210181N10. Registered on 20 June 2017.

**Electronic supplementary material:**

The online version of this article (10.1186/s13063-018-3014-8) contains supplementary material, which is available to authorized users.

## Background

Non-alcoholic fatty liver disease (NAFLD) includes a disease spectrum ranging from simple steatosis to non-alcoholic steatohepatitis (NASH), liver fibrosis, cirrhosis, and hepatocellular carcinoma [1]. It is now present in 15–30% of Asians, has a worldwide distribution, and associates with central adiposity, obesity, insulin resistance (IR), metabolic syndrome, cardiovascular diseases (CVD), and type 2 diabetes [2–4]. It occurs in individuals whose alcohol consumption is insignificant (< 10 g per day for women, < 20 g per day for men) and is characterized histologically by at least 5% steatosis and other parenchymal changes, ranging from inflammation to hepatocyte apoptosis/necrosis and to fibrosis [5]. Excessive hepatic fat and visceral adipose tissue mass are also positively associated with systemic inflammation, lipid metabolism disorders [6], serum insulin, free fatty acids, blood glucose, and IR in that each of these causes increased production of inflammatory factors such as TNF-α and oxidative stress [7–9]. C-reactive protein (CRP), TNF-α, and other acute-phase proteins are increased in NAFLD and there is a strong, graded relationship between the histological severity of NAFLD and these markers [10]. The severity of fatty liver is positively correlated with visceral fat accumulation and insulin resistance and may contribute to higher serum liver tests (aspartate transaminase [AST], alanine transaminase [ALT], alkaline phosphatase [ALP], and gamma-glutamyl transferase [GGT]) [11]. There is no precise consent on the effects and features of an optimal nutritional strategy in NAFLD [12]. Common medical interventions include diet therapy to reduce weight, improved nutritional patterns, physical activity, and supplements such as vitamin E and polyunsaturated fatty acids. The goal of each of these interventions is to reduce fat accumulation in the liver or to increase the antioxidant defense [13]. Weight loss may improve NAFLD: although a ≥ 5% weight loss ameliorates steatosis and cardio-metabolic variables, a ≥ 7% weight loss also improves histological disease activity in NASH [14]. Carbohydrate-rich diets increase abdominal fat deposition, free fatty acids, metabolic syndrome, IR, and diabetes [15–19], and associate with obesity [20, 21]. Several mechanisms have been suggested for the potential effects of a high protein diet (HPD; 25–35% of total energy expenditure) versus a normal protein diet (12–18% of total energy expenditure) [22] on NAFLD. Amino acid catabolism is a high energetic process and it is also a well-known fact that taurine increases bile acid conjugation and energy metabolism to prevent diabetes, obesity, and NAFLD [23]. However, well-controlled dietary intervention studies are restricted [24]. β-cryptoxanthin (β-CX) is another component that we want to investigate in this study. β-CX, one of the six major carotenoids routinely measured in human serum (beta-carotene, lycopene, lutein, β-CX, zeaxanthin, and a-carotene), is obtained primarily from citrus fruits [25]. β-CX is also prevalent in corn, peas, and some yellow-colored animal products such as egg yolk and butter. There are many health benefits of a high β-CX diet. Having a high dietary β-CX allows any byproducts to be safely dealt with by more efficient antioxidants in neutralizing free radicals [26]. The recent studies have reported the inverse association of serum GGT, ALT, AST, with serum carotenoids in NAFLD [27–29]. The β-CX is inversely associated with oxidative DNA damage, lipid peroxidation and inflammation, GGT, and insulin resistance [30–35].

There are several reasons for doing this study: heretofore, it is unknown why β-CX as a source of carotenoids can prevent and treat NAFLD. Iranians exhibit lower intake of fruit and vegetables (as source of beta-CX) [36] and higher intake of carbohydrates (as an agent of NAFLD) [37], Observational, in vitro, animal models and human studies suggest that β-CX has greater bioavailability and absorption than alpha- and beta-carotene-rich foods [38]. As the effect of a prolonged intake of high dose of β-CX (6 mg) and a HPD (25% protein of total calorie intake) on NAFLD has received little research attention, a lack of optimal macronutrient ratios without energy restriction, few long-term studies up to now, and few clinical trial studies, we decided to design a clinical RCT to evaluate the effect of a HPD with β-CX supplementation on some metabolic risk factors, oxidative and inflammatory biomarkers, and adipocytokines among NAFLD.

## Methods/design

### Study design

This is a 2 × 2 factorial design that accomplished as a randomized double-blind, placebo-controlled clinical trial. The Standard Protocol Items: Recommendations for Interventional Trials (SPIRIT) 2013 Statement will be followed in this trial (Additional file 1) [36].

### Setting

The proposed clinical trial will be held at the clinic located in the hospital, Ahvaz Jundishapur University of Medical Science, for 12 weeks to assess the efficacy of daily β-CX 6 mg supplementation adjunctive with a HPD in NAFLD individuals. Figure 1 illustrates the overview of the study.

**Fig. 1 Fig1:**
[figure not shown]
Overview of the study

### Participants (inclusion and exclusion criteria)

Patients will be recruited in the study after fulfilling certain criteria, including: overweight and obese (BMI 25–40 kg/m^2^) individuals aged 18–60 years of both genders, existence of NAFLD by ultrasound, NAFLD activity score < 3, and willingness to participate by signing an informed consent document, Patients with viral hepatitis, cirrhosis, Wilson’s disease, pregnancy acute fatty liver, hepatocellular carcinoma, hypothyroidism and a history of chronic liver disease, lipodystrophy, menopause, parenteral nutrition, bladder and bile duct disease, significant weight loss (≥ 10% of body weight in preceding six months) or weight loss due to surgery, congenital metabolic diseases, individuals on antioxidant supplementations, milk thistle, and omega-3 fatty acids in the previous six months, a history of liver-damaging drugs (amiodarone, anti-virus, aspirin, non-steroidal anti-inflammatories, corticosteroids, methotrexate, tamoxifen, tetracycline, valproic acid), alcohol consumption > 20 g/day, calorie intake < 800 kcal or > 4200 kcal a day, pregnancy and lactation, serum ALT levels more than five times the upper limit (maximum limit of 30 for women and 40 for men), or history of cardiovascular and kidney disease (urine analysis albumin ≥ 30 mg/24 h and GFR ≤ 90 mL/min/1.73 m^2^) will be not included.

### Randomization and blinding

Each eligible patient will receive a randomization number which will be determined by a computer-generated schedule. A randomization table will then be generated by the method of random permuted blocks. Persons who will be operationally independent from the study investigator will perform the study randomization. The investigator, clinician prescriber, and patients will be blinded to the treatment condition. To maintain and guarantee blinding, β-CX and placebo will be identical in appearance. Also, all patients will be outpatients and none of the patients will be in contact with each other. Therefore, they cannot compare their diet. Patients’ data collected during this trial will be kept confidential and will be locked in a secure area. Randomization codes of the study will be opened only after all participants complete the study protocol. After the screening phase, participants will be assigned to four equal groups—HPD + placebo; NPD + β-CX; HPD + β-CX; and NPD + placebo (control group)—to receive an outpatient dietary regimen for 12 weeks. The supplements will be bought by Shanghai Tianfu Chemical Ltd. The study will be conducted in accordance with the ethical standards of the responsible Committee on Human Experimentation (institutional and regional) and the guidelines for the design, conduct, and reporting of human intervention studies [37].

### Interventions

According to (SPIRIT) Fig. 2, the study will be conducted for 12 weeks. The visits and the evaluations will be as follows: baseline (visit 0); 0 week; 6 weeks; and 12 weeks. The nutrient goals for the normal protein diet groups are 30% fat, 15% protein, and 55% carbohydrates and for the HPDF are 30% fat, 25% protein, and 45% carbohydrates. The amount of calorie intake will be similar in the four groups and all participants will be instructed to reduce their calorie intake by 500 kcal/day. Throughout this intervention, each patient will be advised not to make any changes in her/his physical activity level (PAL). As the study protocol will require the participants to maintain their pre-study level of physical activity throughout the study period, individuals’ PAL will be assessed at baseline and each follow-up visit using the IPAQ-short form. The supplemented β-CX dose [38, 39] and the recommended protein [17–20, 40] will be set based on previous studies. The placebo will be manufactured to have a similar appearance, shape, weight, taste, and color as the β-CX capsule. The participants will receive either one capsule of β-CX or an identical placebo daily, taken after dinner for a period of 12 weeks.

**Fig. 2 Fig2:**
[figure not shown]
**Schedule for enrollment, intervention, and assessment. ^1^ HPD + β-CX, ^2^ HPD + placebo, ^3^ normal protein diet + β-CX, ^4^ normal protein diet + placebo

### Primary outcome measures

Fasting venous blood samples will be taken from patients on the morning of admission and on day 85. Primary outcomes including serum high-sensitive C-reactive protein (CRP) (μg/mL) and adiponectin (μg/mL) will be measured by high-sensitivity enzyme-linked immunosorbent assay (ELISA) with the following characteristics: hs-CRP (BioVendor, Heidelberg, Germany; #RH961CRP01HR); adiponectin (ALPCO Immunoassays, Salem, NH; #47-ADPHU-E01). Plasma insulin (IU/mL) (Pars Azmoon Co., Tehran, Iran), β-CX (HPLC- Column18), and free fatty acids (NEFA C Assay Kit; Wako Chemicals, Neuss, Germany, respectively) as other primary outcomes will be measured by the colorimetric methods. The enzymatic method (Pars Azmoon2 Co., Tehran, Iran) will be used for measuring serum hepatic enzymes (including ALT, AST, and ALP). IR will be assessed by homoeostasis model-insulin resistance index (HOMA-IR) [41], according to the following formulas: HOMA-IR [42] will be calculated using the formula “fasting insulin value fasting blood sugar level/405,” equivalent to the HOMA-formula: HOMA = fasting serum insulin (μU/mL) × fasting plasma glucose (mM/L)/22.5 [42]. HbA1c will be measured by spectrophotometry using the Biorad1 IN2IT devices. Glycemic status (fasting blood glucose) will be determined by the glucose oxidase/peroxidase (GOD-Perid) method using commercially available kits (Pars Azmoon Co., Tehran, Iran).

### Secondary outcome measures

Weight will be measured to the nearest 0.1 kg without shoes while patients are in light clothing. Height will be measured without shoes, with shoulders in a normal position, and will be recorded to the nearest 0.1 cm. BMI will then be calculated as weight in kilograms divided by height in meters squared. Waist circumference will be measured with a non-elastic tape (SECA 203 by SECA GmbH & Co. KG, Hamburg, Germany) at a point midway between the lower border of the rib cage and the iliac crest at the end of normal expiration. Similarly, the hip circumference also will be measured at the widest part of the buttocks at the intertrochanteric level to the nearest 0.1 cm. All anthropometric measures will be taken by trained research assistants using standard equipment according to the standard guidelines [43]. Systolic (SBP) and diastolic blood pressure (DBP) will be measured after at least a 10-min rest with Omron RS6 (also known as HEM-6221-E; Omron Healthcare Co., Ltd., Kyoto, Japan), which is an electronic oscillometric device for BP measurement at the wrist with a cuff size appropriate for wrist circumferences in the range of 13–21 cm. Bioelectrical impendence analysis (BIA) will be performed to assess body composition (BIM4; Impedimed, Brisbane, QLD, Australia). The other anthropometric indices will be calculated using the following equations: waist-to-hip ratio (WHR) = waist (m)/hip (m); waist-to-height ratio (WHtR) = waist (m)/height (m); waist-to-hip-to-height ratio (WHHR) = WHR/height (m); body adiposity index (BAI) = hip (cm)/height (m)^1.5^–18; body shape index (ABSI) = WC (m)/(BMI^2/3^ × height [m]^1/2^) [44]. In addition, lipid parameters (total cholesterol, triglyceride levels, HDL cholesterol, and LDL cholesterol) will be measured. Cholesterol, triglyceride levels, and HDL cholesterol (HDL-C) will be measured with enzymatic colorimetric assays using commercially available kits (Pars Azmoon Co., Tehran, Iran). LDL cholesterol (LDL C) will be estimated based on the Friedewald equation [45]. The malondialdehyde (MDA) will be measured according to a procedure described by the Satoh method [46].

### Dietary assessments

Individuals provided three days of 24-h recall questioner at the beginning and at the end of the study; data were collected by a professional nutritionist and analyzed by Nutritionist IV software (First Databank, San Bruno, CA, USA) modified for Iranian foods.

### Statistical analysis

Two populations will be used in the analyses. The intention-to-treat (ITT) population includes all patients who will be randomized, while the per-protocol (PP) population includes all individuals who complete the 12-week intervention (i.e. study completers). The data will be checked for plausibility by randomly checking the accuracy and completeness and verifying against source data. The variables will be tested for normality using the Kolmogorov–Smirnov test, the Shapiro–Wilk test, and normality plots. All quantitative data will be reported as mean ± standard deviation. Baseline characteristics of participants will be compared among groups using analysis of variance (ANOVA) for parametric data and the Kruskal–Wallis test for non-parametric data. The primary analysis, comparing the effects of treatment on primary outcomes of fatty liver over 12 weeks, will be conducted using a generalized linear mixed-models procedure. Treatments and time will be included as fixed effects and the interactions between interventions and time will be tested. If significant main effects or interaction effects are observed, post-hoc analysis with Bonferroni adjustments will be performed. Potential confounding factors and effect modifiers (e.g. baseline age and gender, etc.) will be investigated within the model. Logistic regression will be used to test the multiplicative interaction. Rothman’s synergy index, which would be equal to unity under additively, and less than unity when suggesting antagonism, will be utilized to examine the postulated interaction effect of a HPD and β-CX on fatty liver. The secondary analysis, comparing the effects of treatment on secondary outcomes of fatty liver over 12 weeks, will be conducted using the same procedure. Potential confounding factors and effect modifiers will be investigated within the model. Differences between participants who complete and withdraw from the trial will be analyzed using an independent t test or the Mann–Whitney test for continuous variables (e.g. age) and chi-square for categorical variables (e.g. gender). Associations between severity of fatty liver and nutritional status at baseline will be assessed using regression analysis. McNemar’s test will be used to analyze the binary variables before and after the intervention. Our statistical analyses will be performed by using SPSS 21 (IBM, Armonk, NY, USA) and the results will be considered significant at *P* < 0.05.

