### Sample size and sampling

The sample size was calculated based on the primary outcome measures (12-week change in serum adiponectin, CRP, FFA, insulin, serum β-CX, FBS). Using the standard deviations reported in previous studies [17, 20, 47, 48], a maximum sample size of 18 individuals per group will be selected with mean changes of adiponectin as much as 1.3 and standard division of 1.4 g/day and 30% attrition rate. It calculated by pass 11.

To achieve the target sample size, all patients who will come to the gastrology clinic of Ahvaz hospitals will be included in the study if they will be willing to participate in the study considering the inclusion criteria of the study.

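### With only two blood samples, the primary test should be the week-12 comparison adjusted for baseline, and treatment or time main effects should not trigger post-hoc testing

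*Protocol article*

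**What the plan says.** Under Primary outcome measures, the article states: "Fasting venous blood samples will be taken from patients on the morning of admission and on day 85". Under Interventions, the visit schedule is "The visits and the evaluations will be as follows: baseline (visit 0); 0 week; 6 weeks; and 12 weeks". The text gives no blood draw at week 6, and the schedule figure is not available to check.

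Under Statistical analysis, the primary model is a generalized linear mixed model: "Treatments and time will be included as fixed effects and the interactions between interventions and time will be tested". The rule for follow-up testing is "If significant main effects or interaction effects are observed, post-hoc analysis with Bonferroni adjustments will be performed". Secondary outcomes follow the same procedure. On covariates, the article says only "Potential confounding factors and effect modifiers (e.g. baseline age and gender, etc.) will be investigated within the model".

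Under Sample size and sampling, the endpoint is change: "The sample size was calculated based on the primary outcome measures (12-week change in serum adiponectin, CRP, FFA, insulin, serum β-CX, FBS". The inputs are a group size of 18, a mean change in adiponectin of 1.3 and an SD of 1.4, together with a "30% attrition rate". Under Interventions, every arm is told to cut intake by 500 kcal/day.

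**The concern.** With two samples, a time effect can be estimated only if the pre-treatment value is one of the two responses. The article has therefore fixed this part of the model. Two things follow.

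First, the follow-up rule treats three terms alike, although only one of them measures what treatment did. Under randomization the arms do not differ in expectation at baseline. A treatment main effect averaged over both times therefore carries half the day-85 difference, plus half of any chance imbalance at baseline. The time main effect describes what happened to everyone, and a common calorie deficit makes a common change likely whether or not the arms differ.

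Second, the informative term, intervention × time, reduces to comparing changes from baseline. That is unbiased, but it uses the baseline less efficiently than adjustment does.

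At stake are extra routes to a claim for each outcome, and precision that the trial has already paid for by taking the baseline sample.

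**Working it through.** **Inputs.** From Sample size and sampling: difference d = 1.3, SD s = 1.4, n = 18 per group. From Statistical analysis: significance at 0.05, taken as two-sided. Assumptions: 1.4 is the SD of the 12-week change; equal variance at both times; baseline to day-85 correlation ρ, which the article does not give, between 0.3 and 0.8.

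**The plan's own figure.** n = 2(1.96 + 0.842)² × 1.4² / 1.3² ≈ 18.2, so 19 per group (20 with the t distribution) at 80% power. The article states no power, but its 18 is within two patients of this. At n = 18, SE = 1.4 × √(2/18) = 0.467 and power = Φ(1.3/0.467 − 1.96) ≈ 80% (77% with t). The stated size therefore fits a comparison of change between two arms.

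**Three contrasts.** The SD of a single value is σ = s/√[2(1 − ρ)].

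- Intervention × time (change): effect d, variance s².
- Baseline-adjusted: effect d, variance σ²(1 − ρ²) = s²(1 + ρ)/2.
- Treatment main effect (average of both times): effect d/2 = 0.65, variance σ²(1 + ρ)/2.

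Each SE is the SD × √(2/18), and power = Φ(effect/SE − 1.96).

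| ρ | Variance, adjusted ÷ change | SE change | SE adjusted | Power, change | Power, adjusted | Power, main effect | n per arm for 80%, adjusted |
|---|---|---|---|---|---|---|---|
| 0.3 | 0.65 | 0.467 | 0.376 | 80% | 93% | 53% | 12 |
| 0.5 | 0.75 | 0.467 | 0.404 | 80% | 90% | 36% | 14 |
| 0.7 | 0.85 | 0.467 | 0.430 | 80% | 86% | 22% | 16 |
| 0.8 | 0.90 | 0.467 | 0.443 | 80% | 84% | 15% | 17 |

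**The follow-up rule when the arms do not differ.** With equal variances, change and average are uncorrelated, so the tests are close to independent. Accepting either the treatment main effect or the interaction gives 1 − 0.95² = 9.75%. Adding the time effect, with no common change, gives 1 − 0.95³ = 14.3%.

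A simulation (20,000 runs, four arms of 18, ρ = 0.5 and 0.7, no treatment difference) agrees:

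- The rule permits post-hoc testing in 14% to 15% of trials with no common change, about 60% with a common change of 0.35, and 99% with 0.7.
- Bonferroni tests of all six pairs, made on change only: familywise error 3.7% to 4.3% per outcome.
- Pairwise claims allowed from change, average or day-85 value: 8% to 10%.
- A claim allowed from either the treatment main effect or the interaction: about 10%.

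**The case against.** The strongest reply is that the plan already contains a correct test. A reader might infer from the follow-up rule that the wrong contrast is tested. The documents do not support that: intervention × time is tested explicitly, and with two times it is the between-arm difference in change, the endpoint used for the sample size. Nor is the baseline wasted; it enters through the change score.

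A reader might also infer that a common time trend will be reported as a treatment effect. The article does not say which comparisons follow which term. After a time effect, the usual follow-up compares times, not arms. Even if arms are compared, Bonferroni tests on change stay near 4%. The 10% figure applies only if a claim may rest on more than one term, which the article neither states nor excludes. The low power of the treatment main effect would matter only if the interaction were set aside.

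The covariates named are examples and do not show that the baseline value was ruled out; a fuller list may sit in an analysis plan.

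On size, the gain shrinks as ρ rises, and it is smaller at the factorial margins. With 92/4 = 23 per arm and 30% lost, about 16 per arm remain. If there is no interaction, 32 against 32 gives SE 0.35 and power of about 96% for change, against 98% to 99% adjusted at ρ 0.7 to 0.5.

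All of this stands. It does not answer why two terms that do not isolate the treatment effect should trigger testing at all, or why the less precise of two valid analyses should be kept.

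**Conclusion.** This is a free improvement, not an error that invalidates the plan. The plan has a valid treatment test, uses it less efficiently than it could, and sets two uninformative triggers beside it.

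Adjusting for baseline cuts variance by 35% to 10% for ρ from 0.3 to 0.8. For two arms of 18, power rises from about 80% to between 93% and 84%. The variance ratio (1 + ρ)/2 needs equal variances at the two times but does not depend on 1.4 being the SD of change; the power figures do.

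The false-positive rate is about 10% per outcome if either the treatment main effect or the interaction may support a claim, and near 4% if post-hoc tests are confined to change. The wording leaves both readings open.

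A blood draw at week 6, if the missing figure shows one, would alter the numbers. The treatment main effect would still average in a pre-treatment value.

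**What to change.** State that the only primary test for each outcome is the set of week-12 treatment contrasts (high-protein diet, β-CX and their product), adjusted for that outcome's baseline value. Delete the treatment and time main effects as triggers for post-hoc testing, and say that any pairwise comparisons are made on this same adjusted week-12 scale.

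Preferably fit this as a mixed model with baseline means constrained equal across arms: keep time and treatment × time, and leave out the treatment main effect. Randomized patients without a day-85 sample then stay in the analysis. A plain regression of the day-85 value would drop them unless values were imputed, which sits badly with an intention-to-treat population of everyone randomized and 30% expected attrition.

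The cost is a few sentences in the analysis section. The baseline sample is already taken, and no visit, assay or patient is added. The trial is described as ongoing, with codes to be opened only after all participants finish, so the change should be recorded before then.

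### Single-step Bonferroni after a loosely worded trigger is valid but conservative; a between-arm gate with a step-down would gain about 4 to 12 points of power per comparison

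*Protocol article*

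**What the plan says.** The Study design section states "This is a 2 × 2 factorial design", and under Randomization and blinding "participants will be assigned to four equal groups". For the primary analysis, the Statistical analysis section specifies a generalized linear mixed model: "Treatments and time will be included as fixed effects and the interactions between interventions and time will be tested". It continues: "If significant main effects or interaction effects are observed, post-hoc analysis with Bonferroni adjustments will be performed". The only significance level given is "the results will be considered significant at *P* < 0.05".

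Two things are left open. The number of comparisons that Bonferroni covers is not given; four groups make 4 × 3 / 2 = 6 pairs, so six is an inference. No single overall test of the four groups is named as the trigger either. As written, any main effect or interaction will do, and time is one of the main effects.

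Sample size and sampling sets the target at 18 per group. Its planning inputs are "mean changes of adiponectin as much as 1.3 and standard division of 1.4 g/day and 30% attrition rate".

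**The concern.** Bonferroni over six pairs tests each at 0.05/6 whatever the other pairs show. That ignores two facts. First, pairwise hypotheses among four means are logically linked: once any pair is known to differ, at most three of the six equalities can still be true (three groups alike, one different). Second, if an overall between-arm test has already rejected equality of all four groups, that limit applies from the first comparison on. A step-down procedure uses these facts and keeps the same 5% guarantee with larger per-comparison levels.

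At stake is the chance of detecting the group differences that the trial wants to report (combination, diet alone or supplement alone against control). With 18 per group, sized for one unadjusted comparison, little power is left to give away.

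**Working it through.** **Inputs.** Difference 1.3, SD 1.4, 18 per group, 30% attrition (Sample size and sampling); 92 patients (Abstract), so 92/4 = 23 per group; alpha 0.05. Assumed: two-sided tests, equal variances, 80% power behind the stated 18 (power is not given), and the 12-week change analysed as a one-way comparison of four groups in place of the full mixed model.

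**The plan's own figure.** n = 2 × (1.960 + 0.842)² × (1.4/1.3)² = 2 × 7.85 × 1.160 = 18.2, or 19 after rounding up; the t-based answer is 20. Both are within 2 of the stated 18. The 18 therefore matches one comparison at unadjusted 0.05.

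**Power of one pair at 18 per group.** The standardised difference is 1.3 / (1.4 × √(2/18)) = 2.786.

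| Level | Normal approximation | Pooled t, 68 df |
|---|---|---|
| 0.05 | 79.6% | 78.4% |
| 0.05/3 = 0.0167 | 65.2% | 63.0% |
| 0.05/6 = 0.0083 | 55.9% | 53.0% |

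**Whole procedures.** Simulation with 200,000 trials per setting, 18 per group, one group different by 1.3. The gate is the 3-df between-arm test at 0.05.

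| Procedure | Power per pair |
|---|---|
| Bonferroni/6, no gate | 53.0% |
| Gate + Bonferroni/6 | 52.8% |
| Holm, no gate | 55.9% |
| Shaffer (divisors 6,3,3,3,2,1), no gate | 59.8% |
| Gate + Shaffer (divisors 3,3,3,3,2,1) | 61.4% |

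The gate itself costs 53.0 − 52.8 = 0.2 points here, and at most about 1 point in any pattern tried. Replacing single-step Bonferroni with ungated Shaffer gains 59.8 − 53.0 = 6.8 points. Adding a proper gate gains a further 61.4 − 59.8 = 1.6. So most of the loss comes from dividing by six at every step.

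**How the gated gain varies** (gate + Shaffer minus gate + Bonferroni/6):
- One group different: +8.6 points at 16 per group (30% loss from 23 leaves 23 × 0.7 = 16.1) and +7.7 at 23.
- Two groups against two: +8.5 to +9.8 for 16 to 23 per group.
- Additive effects of 1.3 per factor: +10.5 to +12 for the contrasts of 1.3.
- Additive effects of 0.65 per factor, so that only combination against control reaches 1.3: about +4 to +6.

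**Family-wise error within one outcome, 18 per group.**

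| True pattern | Gate + Bonferroni/6 | Gate + Shaffer |
|---|---|---|
| All four equal | 0.038 | 0.048 |
| Three equal, one different | 0.022 | 0.043 |
| Two equal pairs, far apart | 0.017 | 0.050 |

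**The trigger as worded.** All groups are told to cut 500 kcal/day (Interventions), so a time effect with no difference between groups is plausible. With all groups equal and the trigger opened by time, a first step at 0.05/3 gives 7.6% error. If any one of three factorial effects, each tested at 5%, opens it (which happens 14.2% of the time), the error is 6.8%. Bonferroni/6 stays at about 4% in both cases.

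**The case against.** A reader might infer that the plan pays for multiplicity twice, once through the trigger and once through the division by six. The figures do not support that: the trigger costs at most about 1 point.

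A reader might also infer that Bonferroni buys nothing the trigger does not already give. That is wrong for the trigger in the document. A significant time effect says nothing about whether the groups differ, so all six equalities may still be true, and it is Bonferroni that holds the error rate there.

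The family of six is inferred, and a condensed article may leave it to the analysis plan. If only the three comparisons with control are meant, Bonferroni already uses 0.05/3. After a significant overall between-arm test at most two of those three equalities can be true, so 0.05/2 is available. In simulation at 18 per group the gain over ungated Bonferroni/3 or its gated form is then smaller, about 4 to 8 points (for example 0.615 to 0.658 with one group different), with error still within 5%.

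Single-step Bonferroni has matching simultaneous intervals and a step-down has no simple ones, so the exchange is not free. In the 2 × 2 factorial, a two-level diet or supplement main effect needs no pairwise step at all. These objections limit the point. They do not remove it, because the improvement holds once the gate is restated, and an ungated step-down improves on single-step Bonferroni even if it is not.

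**Conclusion.** The plan contains no error here. Within an outcome its rule controls the family-wise rate and is conservative. On the inferred family of six pairs, a step-down keeps 5% and raises power per pair from about 0.53 to 0.56 (Holm), 0.60 (Shaffer) or 0.61 (Shaffer behind a single between-arm gate), with one group different by 1.3 at SD 1.4 and 18 per group. The gated gain is about 4 to 12 points over the patterns and group sizes tried.

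The smaller divisors are safe behind one overall between-arm test and not behind the present trigger. The 5% is per outcome: the sample size section lists six outcomes, each tested at 0.05, and neither the present rule nor the replacement controls error across them. The figures rest on the assumptions listed with the inputs. This is a cheap improvement worth making, of moderate weight.

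**What to change.** Replace the post-hoc sentence with: *If the 3-df between-arm test (intervention × time) for an outcome is significant at 0.05, the six ordered unadjusted pairwise p-values are compared with 0.05/3, 0.05/3, 0.05/3, 0.05/3, 0.05/2 and 0.05, stopping at the first that fails.*

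- State the family. If it is the three comparisons with control, use 0.05/2, 0.05/2 and 0.05 behind the same gate.
- The primary-outcome blood samples are taken at two times, so intervention × time has (4 − 1) × (2 − 1) = 3 df. For any outcome also measured at week 6, define the gate as the 3-df test of the 12-week change.
- If the present trigger is kept, use an ungated step-down: Holm, or Shaffer with divisors 6, 3, 3, 3, 2, 1.
- Say that the diet and supplement main effects are two-level contrasts without pairwise adjustment.
- Report 95% confidence intervals and label them as unadjusted.

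The cost is a sentence or two in the plan and the loss of simple matching simultaneous intervals; no patients are added. The article describes the trial as ongoing, with randomization codes closed until all participants finish, so the change can be fixed before unblinding.
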